## Interventions

### Standard training and mental healthcare implementation (control arm)

#### Primary care level

Primary care workers will be trained to screen, assess, diagnose, and treat psychosis and related disorders using the WHO mental health Gap Action Programme Intervention Guide (mhGAP-IG, version 2.0) [38]. The mhGAP-IG has been used as a package for providing mental health care in LMIC settings including Uganda [39]. This 5-day training, coordinated by YouBelong Uganda in collaboration with Butabika National Mental Hospital and the Ministry of Health in Uganda, will be delivered by psychiatrists and/or psychiatric clinical officers trained as mhGAP-IG trainers. Training will be delivered primarily in English. After the training, the primary care workers will receive monthly supervision from a psychiatric clinical officer or psychiatric nurse. This is comparable to the standard procedures used nationally for training primary care workers in mental health.

### Community level

At the community level, community health workers will receive a 2-day training based on the WHO mhGAP Community Toolkit Community Provider manual [40] to increase knowledge and skills required to identify symptoms of psychosis and other mental health problems. Additionally, they will be trained to disseminate information on psychosis at community awareness-raising meetings**.** The training will be delivered in Luganda, the predominant local language, by the trained primary care workers and experienced trainers from the YouBelong Uganda team in collaboration with Butabika Hospital. Community health workers will also receive monthly supervision by trained primary care workers after the training.

### SCAPE-U (intervention arm)

The initial SCAPE-U intervention was developed through an 18-month contextualisation phase, consisting of theory of change workshops, a single-arm small-scale pilot study (involving one cluster, 9 SCAPE-U facilitators and 10 service users) and qualitative interviews. The final SCAPE-U intervention to be tested in the feasibility trial was designed based on findings from the contextualisation phase.

Figure 1 provides an overview of the participation of SCAPE-U facilitators across the tiers of primary care, community, and home-based care. SCAPE-U facilitators will receive a travel compensation for attending facilitator/PhotoVoice training, health worker training, and home visits. However, they will not receive a salary.

### SCAPE-U facilitator training

The training will prepare selected people with lived experience of psychosis, and the YouBelong community recovery program, to participate in primary care and community health worker training and to conduct home visits; they will be trained in PhotoVoice and hereafter referred to as SCAPE-U facilitators. PhotoVoice is based on participatory methods where photography is a medium of storytelling and message delivery [41–43]. SCAPE-U facilitators will use PhotoVoice narratives to cofacilitate training of PHWs and CHWs, as well as provide psychosocial support during home visits. The training, which will be delivered in Luganda, will involve a 2-day residential, followed by eight weekly sessions. SCAPE-U facilitators will learn about using cameras and taking pictures, writing recovery stories, practicing storytelling using photographs, public speaking, advocacy, addressing stigma, and managing confidentiality and disclosure. PhotoVoice has successfully been used to reduce stigma among persons living with severe mental health conditions and to facilitate peer support and community reintegration in the USA [44, 45]. The approach has also been tested through a pilot study in Nepal where people with lived experience of depression, psychosis, and alcohol use disorder participated in mhGAP-IG trainings of primary care workers [46, 47]. Findings from this study suggested this approach to training improved diagnostic accuracy and decreased stigma amongst primary care workers [22]. Details of the PhotoVoice training are described elsewhere [43].

### Primary care level

Primary care workers and community health workers will receive training with the same duration and broad content as the standard implementation (control) arm. However, in the intervention arm, SCAPE-U facilitators will co-facilitate trainings alongside mental health professionals. During the primary care worker training, SCAPE-U facilitators will present sessions on living with psychosis, using their PhotoVoice stories. SCAPE-U facilitators will describe the symptoms of psychosis from an experiential perspective, specifically the experience of suffering, negotiating pathways of care and treatment, including an emphasis on the benefit of psychosocial support in addition to medication. SCAPE-U facilitators will also conduct question and answer sessions so that primary care workers can ask them about their experiences. In addition, SCAPE-U facilitators will be present during the other training sessions so that primary care workers can interact with them in both structured and unstructured social activities. At the conclusion of the training, SCAPE-U facilitators will hold a session on anticipated challenges of primary care workers, and with the primary care workers, they will collaboratively come up with solutions to address these challenges. SCAPE-U facilitators will also collaborate in the supervision of primary care and community health workers after their trainings are completed.

### Community level

In addition to standard training, community health workers in the intervention arm will receive an added component in which SCAPE-U facilitators present recovery narratives, aimed at improving the accuracy of identifying individuals with possible psychosis within their communities. The narratives will incorporate elements of early detection, referral, and care, along with stigma reduction. The aim of the SCAPE-U facilitators’ participation is to motivate community health workers to strengthen the linkage and referral between community and primary healthcare services. SCAPE-U facilitators will also participate in supervision sessions with the community health workers after their training to help raise issues about the community and other aspects of the care pathway.

### Home level

Service users receiving service from the health facilities in the control arm will not receive any additional service besides that provided from health facilities. For those receiving service from the intervention arm and diagnosed with psychosis, SCAPE-U facilitators will conduct five 1-h home visits to service users who have been diagnosed with psychosis by primary care workers and are currently receiving treatment. Primary caregivers to service users are expected to be present during these visits. Each session will consist of SCAPE-U facilitators sharing their lived experiences through a 10-min presentation of an aspect of their PhotoVoice story. Each session will be tailored to a psychosocial theme (medication adherence, conflict resolution, stigma, livelihood support, and dealing with challenging behaviors) [33, 35]. There will then be time for questions and discussion with the service users and their family (Table 2).

**Table 2 Tab2:** Overview of services and implementation by study arm and level of care

Care level	Standard services arm	SCAPE-U arm
Primary care	mhGAP-IG training conducted by a psychiatrist and/or psychiatric clinical officer for 5 days with a focus on psychosis diagnosis and treatment	mhGAP-IG training conducted by a psychiatrist or psychiatric clinical officer combined with a SCAPE-U facilitator (people with lived experience of psychosis) presenting recovery stories and other activities
Community	2-day training conducted by trained psychiatric clinical officer or psychiatric nurse on identification and referrals of people potentially experiencing psychosis	2-day training conducted by trained psychiatric clinical officer or psychiatric nurse, combined with SCAPE-U facilitator presenting recovery stories and other activities
Home	No services	5 fortnightly sessions of psychosocial support provided by SCAPE-U facilitators using PhotoVoice narratives based on themes in the YouBelongHOME intervention

### Supervision of SCAPE-U facilitators

Supervision meetings with SCAPE-U facilitators will involve both technical supervision (relating to sharing of stories using PhotoVoice during training and home visits) and supportive supervision, which will focus on addressing any emotional, social, or economic challenges faced by the facilitators. The supervisors will be members of the YouBelong team. Once a month, each SCAPE-U facilitator will receive 1 h of group supervision and 30 min of individual supervision at the health facility. This will be an opportunity for the SCAPE-U facilitators to provide feedback from their experiences working with health workers and conducting home visits. This will provide a feedback channel to the primary care workers about these other aspects of the care system.

### Randomization and blinding

Randomization of clusters in the feasibility trial will be completed prior to participant recruitment and will be conducted by an independent statistician using Stata. Covariate-constrained clusterrandomisation will be used to assign health facility clusters to study arms while ensuring balance across key variables {Hemming, 2023 #120}[48]. Covariate-constrained randomization is a form of restricted randomization; specifically, the randomization will be constrained on two characteristics: number of health facilities per arm, and rural vs. urban location.

Constrained randomisation helps prevent baseline imbalances that can occur by chance, particularly in studies with a limited number of clusters, such as feasibility trials [48]. For logistical reasons, research assistants/data collectors will not be blinded. PCWs and CHWs will be blinded to the arm allocation. We will have separate mhGAP-IG trainers for each arm, and these will be blinded. Because SCAPE-U facilitators will be engaged only in the intervention arm, and only service users accessing care at PHCs in the intervention arm will receive the home visit intervention, they will both be blinded by the cluster randomized nature of the trial.

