
### Recruitment

Potential SCAPE-U facilitators will be identified and contacted by the YouBelong team. Potential service users’ participants will be identified by primary care workers working in participating health facilities. Their identification will commence after training of primary care and community health workers is complete. Following diagnosis of a service user with psychosis, as part of their usual practice, the primary care worker will contact the research assistant by telephone. The research assistant will either immediately attend the facility or arrange an alternative time to meet with the service user. Eligibility of service users will be assessed by research assistants, who will be psychiatric clinical officers by training. The research assistant will complete a screening assessment, including assessment of decision-making capacity using the University of California, San Diego Brief Assessment of Capacity to Consent (UBACC) [36]. Eligible potential participants will be given information about the study. Informed consent will be obtained for participants who are eligible and interested in participating. For all consenting participants, detailed contact information will be recorded.

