Knowledge of psychosis diagnosis and treatment	mhGAP Knowledge	Self-report knowledge test	Primary care workers	Pre- and post-training, and at final supervision session
Clinical diagnosis skills in structured role plays	ENACT	Structured observational rating scale	Trained raters	Pre- and post-training, and at final supervision session
# of individuals diagnosed with psychosis	Health facility records	Medical records	Research assistant reviewing clinical records	Pre- and post-training, and at final supervision session
Fidelity of treatment to mhGAP guidelines	Fidelity Checklist	Observer completed fidelity checklist	Observations	Pre- and post-training, and at final supervision session
Accuracy of diagnosis (confirmatory diagnosis with SCID by PCO)	DSM-V psychosis module (SCID)	Structured clinical interview	Psychiatric clinical officer	Pre- and post-training, and at final supervision session

For primary care workers, the outcomes include attitudes measured through the Social Distance Scale (SDS) [57], knowledge measured through the mhGAP Knowledge assessment [58, 59], clinical competency measured through ENACT [60], fidelity of treatment measured through the fidelity checklist, and number of diagnosis data coming from health facility records. To determine diagnostic accuracy, a psychiatric clinical officer will use the SCID [61] to determine the diagnosis of a subset of service users diagnosed by the primary care workers. The psychiatric clinical officer’s diagnosis will be taken as the gold standard and matched with the primary care workers’ diagnosis.

Community health worker outcomes will include attitudes towards people with mental health conditions measured through the Social Distance Scale (SDS) [57] and data on number of referrals to primary care, and accuracy of psychosis detection derived using health facility data.

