Timelines for quantitative data collection are presented in Table 4. Data will be collected by research assistants at the training site, health facility, or at the participants’ home. Study data will be collected and managed on Android tablets using REDCap (Research Electronic Data Capture) electronic data capture tools hosted at Infectious Disease Institute, Uganda. REDCap is a secure, web-based software platform designed to support data capture for research studies, providing (1) an intuitive interface for validated data capture; (2) audit trails for tracking data manipulation and export procedures; (3) automated export procedures for seamless data downloads to common statistical packages; and (4) procedures for data integration and interoperability with external sources [62]. Participants will receive 10,000 Ugandan shillings (US$ 2.70) for each completed assessment to compensate for time and travel costs (Table 5).

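### The blanket rule that data collectors are unblinded makes no exception for the rater-judged worker outcomes (ENACT and the SCID reference diagnosis), and nothing requires the SCID assessor to be independent of the worker being judged

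*Protocol article*

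**What the plan says.** All references are to the protocol article.

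- **Blinding.** Randomization and blinding gives one rule for everyone who collects data: "For logistical reasons, research assistants/data collectors will not be blinded". No outcome is exempted. The same section says that the mhGAP-IG trainers are separate for each arm and are blinded. That covers trainers, not assessors.
- **Who collects data.** The section on measures and outcomes says: "Data will be collected by research assistants at the training site, health facility". Recruitment adds: "Eligibility of service users will be assessed by research assistants, who will be psychiatric clinical officers by training".
- **ENACT.** Table 4 lists the outcome as "Clinical diagnosis skills in structured role plays", measured before training, after training and at the last supervision session. The source is given only as "Trained raters".
- **SCID.** The text below Table 4 says that "a psychiatric clinical officer will use the SCID [61] to determine the diagnosis of a subset of service users diagnosed by the primary care workers". That officer's diagnosis is the gold standard against which the worker's diagnosis is compared.
- **The same cadre in other roles.** Study participants lists three psychiatric clinical officers among the specialists who train the primary care workers. The control-arm description, Primary care level, says that after training "the primary care workers will receive monthly supervision from a psychiatric clinical officer or psychiatric nurse". Possible harm and safety also names psychiatric clinical officers as supervisors of these workers.
- **Use of the estimates.** The Abstract says that individual-level data on workers and service users are collected partly to obtain effect sizes. Data analysis says that descriptive statistics for all quantitative outcomes will feed the power analyses of a definitive trial.

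**The concern.** ENACT and the SCID are structured instruments, but each ends in a judgement by the person applying it. If that person knows the arm, expectation can shift the score, and the shift adds directly to the difference between arms. The SCID raises a second issue. As the protocol stands, the officer who trained or supervises a worker is not excluded from supplying the reference diagnosis for that worker's patient.

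The stated reason, logistics, is easy to accept for interviews in homes and facilities. It does not obviously apply to a staged role play, which can be recorded and scored elsewhere, or to the choice of which officer does a given SCID.

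At stake are secondary estimates that the pilot intends to hand to the next trial. Sampling error shows in a confidence interval; rater bias does not, and a later team reading the pilot report could not see or remove it.

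**Working it through.** The plan gives no figure to reproduce on this point. The check is who rates what, followed by an illustration of scale.

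**1. Is each rater covered by the unblinded rule?** The rule names research assistants and data collectors, and the measures section has research assistants collect the data, including at the training site and health facility. On that reading the rule reaches both outcomes. It does not name the ENACT raters or the SCID assessor, so their status follows from the general sentence.

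**2. Is each rater from the trainers' and supervisors' cadre?**
- SCID assessor: yes, explicitly. The assessor is a psychiatric clinical officer, and so are some trainers and supervisors.
- ENACT raters: not stated. The link could only be inferred by combining the description of research assistants in Recruitment with the general statement on data collection.

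**3. Is independence required?** No sentence says that the SCID assessor is a trainer or supervisor of the worker being judged, and none says otherwise.

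**4. Could a trainer or supervisor who also rates know the arm?** In the intervention arm, people with lived experience co-facilitate training and join supervision (SCAPE-U, Primary care level), so an officer in those roles would see the intervention. Because trainers are separate by arm, differences between raters would also be confounded with arm if a training officer did the SCIDs for that arm.

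**5. Scale for ENACT (illustration).**

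From the document: 36 workers per arm and 6 facilities × 2 workers = 12 per cluster. Assumed: ICC 0 to 0.10, and pre-post correlation r of 0.3 to 0.5.

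SE of the arm difference, in SD units = √[(2/36) × (1 − r²) × (1 + 11 × ICC)]

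| ICC | r | Calculation | SE |
|---|---|---|---|
| 0 | 0.5 | √(0.0556 × 0.75 × 1.00) | 0.204 |
| 0.05 | 0.5 | √(0.0556 × 0.75 × 1.55) | 0.254 |
| 0.10 | 0.3 | √(0.0556 × 0.91 × 2.10) | 0.326 |

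An assumed bias of 0.25 SD is therefore 0.25/0.326 = 0.77 to 0.25/0.204 = 1.23 standard errors.

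**6. Scale for a later sample size (illustration).** Required size is proportional to 1/effect². With an assumed true effect of 0.30 SD and bias b, a trial sized on the observed effect is too small by ((0.30 + b)/0.30)²:
- b = 0.10: (0.40/0.30)² = 1.78
- b = 0.20: (0.50/0.30)² = 2.78
- b = 0.25: (0.55/0.30)² = 3.36

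A direct calculation (two-sided 5%, 80% power, no clustering) agrees. A true effect of 0.30 needs 175 per arm. Planning on 0.40 or 0.50 gives 99 or 63 per arm, with true power of 56% or 39%.

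Bias could run the other way. With b = −0.10 the later trial would be too large by (0.30/0.20)² = 2.25.

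No comparable figure is possible for the SCID, because the article does not give the size of the verified subset.

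**The case against.** Several stronger readings are tempting, and the document does not support them.

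- **That ENACT raters come from the training cadre and know the arm and time point.** Table 4 says nothing of their profession, independence or masking. It lists trained raters, the psychiatric clinical officer and research assistants as separate sources, so it is even arguable whether the unblinded rule covers the first two. The general statement on data collection points to its covering them, but this remains an inference.
- **That supervisors judge their own trainees.** Same cadre is not same person. Trainers and research assistants are named as separate groups for end-of-study interviews. Staff assignment is also detail that an article may leave to the full protocol.
- **That the estimates are biased upward by a known amount.** The document gives neither size nor direction, and every bias figure above is assumed. The 0.25 SD example is about one standard error, so it is no larger than this pilot's own sampling noise. Knowledge of time point affects both arms and largely cancels from the arm difference unless it acts differently by arm.
- **That the definitive trial will be sized on ENACT or SCID.** No sentence says so. Data analysis sets out a modelled arm comparison only for PANSS, and Sample size disclaims a power calculation and formal testing.

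These points limit the claim but do not remove it. Blinding is a design rule that the article does state, and it states it without exception. Disclaiming hypothesis tests does not protect an estimate that is meant for reuse.

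**Conclusion.** The point holds in limited form. A blanket no-blinding rule, with no exception for rater-judged worker outcomes and no independence requirement for the reference diagnosis, leaves the secondary ENACT and diagnostic-accuracy estimates at risk of rater bias of unknown size and direction. Shared cadre is explicit for the SCID and unstated for ENACT.

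The sample-size factors of 1.8 to 3.4 are illustrations. They assume a true effect of 0.30 SD, upward bias of 0.10 to 0.25 SD, and a later trial sized on the observed effect.

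The progression criteria (recruitment, retention, contamination, cluster comparison, missing data, safety) use neither outcome, so the decision to proceed is untouched. The change is still worth making now, because testing data-collection procedures is itself a pilot objective. The observer-completed fidelity checklist in Table 4 has a similar exposure and should be considered at the same time.

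**What to change.** In Randomization and blinding, keep the unblinded interviews but exempt the two outcomes:

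1. **ENACT.** Record the role plays. Have the existing trained raters score them later in random order, masked to arm and as far as possible to time point, with each rater scoring both arms.
2. **SCID.** Assign it to a psychiatric clinical officer already on the study who neither trained nor supervised that worker, did not enrol that service user, and is not told the facility's arm.
3. **Reporting.** Where masking proves impossible, report the estimate as at risk of rater bias.

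The cost is modest but real: consent to record, handling of up to 72 workers × 3 time points = 216 recordings, later ENACT scores, and a scheduling constraint among clinical officers. Only three are listed in training delivery, and the article does not say how many others there are. No extra rater role or visit is added. Masking of the SCID may still fail if service users mention home visits, so any unmasking should be recorded.

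### The protocol calls health workers, trainers, facilitators and service users blinded, but the SCAPE-U intervention is overt to all who deliver or receive it, and recruiting users after arm-specific training leaves between-arm estimates open to bias

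*Protocol article*

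**What the plan says.** The section Randomization and blinding makes four statements about masking:

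- Health workers: "PCWs and CHWs will be blinded to the arm allocation".
- Trainers: "We will have separate mhGAP-IG trainers for each arm, and these will be blinded".
- Facilitators and service users: "they will both be blinded by the cluster randomized nature of the trial".
- Assessors: "For logistical reasons, research assistants/data collectors will not be blinded".

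The same section fixes the order of events: "Randomization of clusters in the feasibility trial will be completed prior to participant recruitment". Under Recruitment, potential service users "will be identified by primary care workers working in participating health facilities", and this starts only once both cadres of health worker have been trained. Research assistants then assess eligibility.

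Under SCAPE-U (intervention arm), Primary care level, the text says that "in the intervention arm, SCAPE-U facilitators will co-facilitate trainings alongside mental health professionals". Facilitators also attend the remaining sessions of the primary care worker training and take part in later supervision. The Community level section adds their recovery narratives and supervision role for community health workers. The Home level section and Table 2 give intervention-arm users five home sessions and control-arm users none.

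**The concern.** A statement that a group is blinded tells the reader that its behaviour and reports cannot depend on knowing the arm. Here that assurance covers the people who decide which users enter the study and the people who report most of the outcomes. If it is wrong, two risks go unacknowledged.

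The first is identification bias. Users come in through workers whose recognition of psychosis the intervention is meant to change, so the two arms may enrol different kinds of user. The second is reporting bias. The Social Distance Scale asks workers about their attitudes to people with psychosis after training that, in one arm, such people helped to lead. Users who received home visits from peers report their own symptoms, quality of life and stigma.

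Data analysis reads the between-arm PANSS difference as a potential effect size, and Sample size says that pilot estimates will inform the full trial. An error about blinding could therefore carry over into that trial's design.

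**Working it through.** The point depends on no power or alpha figure. The check sets the blinding text beside the intervention, recruitment and outcome text.

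**1. Who is called blinded, and what they see**

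| Group | Stated status | What the intervention sections describe |
|---|---|---|
| SCAPE-U facilitators | Blinded by the cluster design | They work in one arm only and are its distinguishing component |
| mhGAP-IG trainers, SCAPE-U arm | Blinded | They teach beside facilitators |
| Primary care workers, SCAPE-U arm | Blinded | Facilitators present, answer questions, attend other sessions and join supervision |
| Community health workers, SCAPE-U arm | Blinded | An added narrative component, and facilitators in supervision |
| Service users, SCAPE-U arm | Blinded by the cluster design | Five home visits, after a consent process that explains study procedures |
| Control-arm trainers, workers, users | Blinded | Standard training or usual facility care; they might not know what the other arm gets, but no masking procedure is described |
| Research assistants | Not blinded | They screen users and collect data |

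The reason given for facilitators and users does not follow. Allocating whole clusters can limit contact between arms. It does not conceal an overt component from those who give or receive it. Objective 1 in Table 1 itself asks workers and caregivers whether facilitator involvement is acceptable, which presupposes that they notice it.

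**2. How many are exposed to the overt component** (Study design and Study participants)

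- Facilities per arm: 3 clusters × 6 = 18, of 36.
- Primary care workers: 18 × 2 = 36, of 72.
- Community health workers: up to 18 × 5 = 90, of 180.
- Service users: 3 × 10 = 30, of 60.
- Facilitators: all 8 to 10.

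These agree with the targets that the protocol states.

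**3. The route to identification bias**

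The sequence is: clusters randomised; workers trained by arm; users diagnosed and notified by those workers; users screened by unblinded research assistants; users enrolled and baseline PANSS measured. Study participants makes diagnosis after the trial's mhGAP training an inclusion criterion. Background gives accuracy of diagnosis as a hypothesised effect, and Community level aims to improve case identification. All 60 users therefore enter after a step that the intervention is designed to alter.

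**4. The route to reporting bias**

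In Table 4, service-user PANSS is self-reported or family-reported. WHOQOL-BREF, EQ-5D-5L, DISCUS and the Social Distance Scale are self-reported.

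**5. Size**

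The document gives nothing from which either bias can be estimated. For scale only: assume that a share s of one arm's users are extra cases whose mean severity differs from the rest by d standard deviations. That arm's mean then shifts by s × d. With s from 0.1 to 0.3 and d from 0.5 to 1.0, the shift runs from 0.1 × 0.5 = 0.05 to 0.3 × 1.0 = 0.30 standard deviations. Both inputs are assumptions.

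**The case against.** **Consequence.** The primary outcomes are feasibility, acceptability and safety, formal testing is ruled out, and none of the go/no-go criteria is shown to change. This stands, and it limits the weight of the point. The estimates meant for the full trial are still affected.

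**Monitoring already planned.** Table 4 covers numbers diagnosed and referred, and SCID confirmation is planned for a subset of diagnoses. PANSS is summarised at baseline within each arm, and baseline comparability will be explored. This stands in part. Notified, screened, eligible and enrolled counts by arm are not among these, and the mechanism is not named.

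**Timing of the reveal.** The protocol says when clusters are randomised, not when facilities learn their arm. The statement about workers may be meant for the stage before training. A reader might infer that workers are selected and measured at t2 knowing their arm; the document does not show this. Even on that reading, the blinding could not last beyond the first co-facilitated session.

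**Stronger readings.** A reader might infer that nobody is blinded, that everyone is equally affected, that no outcome has a masked rater, or that the protocol conceals the problem. The text supports none of these. Control-arm people may not know of the other arm, and only half of the workers and users meet the overt component. The masking of the ENACT raters is not stated. The order of randomisation and the unblinded data collectors are disclosed openly.

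**Conclusion.** The blinding statement is wrong as written for facilitators and for SCAPE-U-arm trainers, workers and service users. For control-arm people, the most that can be said is that they may be unaware of the other arm. The contradiction lies within the protocol itself and needs no outside information.

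Service-user case mix can differ by arm, and the self-reported and family-reported outcomes are open to reporting bias. Neither bias can be sized from the document. For self-reported attitudes, social desirability would plausibly favour SCAPE-U. The direction of any case-mix difference is not determined. The feasibility outcomes are less exposed than the between-arm estimates. The conclusion assumes that the intervention is delivered as described and that no masking procedure exists beyond what is stated.

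**What to change.** 1. Replace the blinding text. State that the trial is open-label for those who deliver or receive the intervention, exactly what information is withheld from whom, and whether the ENACT raters are masked. The cost is wording only.
2. Where scheduling allows, do not reveal allocation to facilities and workers until workers are selected, have consented and have completed the t2 pre-training measures. The cost is tighter scheduling of arm-specific training. Because data may be collected at the training site, the t2 measures would have to be completed before facilitators appear there.
3. Beyond the diagnosis, referral and baseline data already planned, report by arm the numbers notified, screened, eligible and enrolled. The cost is a simple log.
4. Present the between-arm PANSS and other service-user differences as open to identification and reporting bias wherever they inform the full trial. Users must be diagnosed after the arm-specific training, so for them this is transparency and does not remove the bias.
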